#### Secondary outcome measures

The secondary outcomes will be: falls, recorded with monthly postal calendars over a period of 12 months; the proportion of people meeting the physical activity guidelines of 150 minutes per week of moderate to vigorous physical activity (MVPA) (intensity defined using the Freedson equation of ≥ 1952 counts/minute from the *Actigraph* to permit comparisons with other studies [18] and we will also examine this outcome using a cut point of 1040 counts/minute which is calibrated to detect MVPA (i.e., ≥ 3.7 METs) in older adults [19]); quality of life, assessed with the EQ-5D [20]; fear of falling, assessed using the short-form Falls Efficacy Scale International [21]; mood, assessed with the positive subscale of the Positive Affect Scale [22]; mobility limitation, assessed using the Late Life Function and Disability Index [23]. All secondary outcomes will be measured at both 6 and 12 months after randomisation with the exception of falls, which will only be measured at 12 months after randomisation. The intervention group will also complete a brief survey of barriers and enablers to ongoing physical activity participation at the 6 month time point.

### Analysis of outcomes

Accelerometer data will be analysed using *ActiLife 6* software. Acceptable wear time will be set a priori and defined as 4 days or more of 10 hours or more per day. General linear models will be used to assess the effect of group allocation on the continuously-scored primary (average physical activity counts per minute) and secondary outcome measures (quality of life, fear of falling, mood, mobility limitation), at both six and 12 months after randomisation, after adjusting for baseline scores.

Between-group differences in mobility-related goal attainment, at both six and 12 months after randomisation, will be analysed with ordinal regression. To aid interpretation of the GAS, the scores will also be dichotomised (goal met versus goal not met), and odds ratios calculated.

The number of falls per person-year will be analysed using negative binomial regression models to estimate the between-group difference in fall rates after one year (secondary outcome). Modified Poisson regression models will be used to compare groups on dichotomous outcome measures (proportion of fallers, proportion meeting physical activity guidelines). All analyses will be pre-planned, conducted while masked to group allocation and will use an intention-to-treat approach.

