### Outcomes

#### Primary outcomes

The four primary outcomes will be: physical activity participation, expressed as mean counts/minute/day, assessed over a 7-day period using a matchbox-sized accelerometer (*ActiGraph* GT3X+), measured at both six and 12 months post-randomisation; and mobility-related goal attainment, assessed using the Goal Attainment Scale (GAS), measured at both six and 12 months post-randomisation [16].

*ActiGraph* GT3X+ is the most researched accelerometer in the physical activity and public health field over the last 15 years and has been shown to be a valid instrument [17]. Participants will be instructed to wear the accelerometer on the right hip, attached via an adjustable elastic belt, for 7 consecutive days during waking hours (except during water-based activities or bathing). Activity counts per second will be collected at a sampling frequency of 30Hz and reintegrated to 60-second epochs for data analysis. The mean counts/minute/day *ActiGraph* measure will be computed as the total counts accumulated in a valid day divided by the wear time of that day. To be considered as a valid day for analysis, *ActiGraph* wear time must include 10 hours or more. Periods of 90-minutes or more of consecutive zeros (indicating non-use) will be considered as non-wear time. Accelerometer data will be manually checked against participant diaries/calendars to verify wear time and erroneous data will be excluded prior to analysis. Physical activity participation will be assessed at both six and 12 months after participant randomisation, and *ActiGraph* data will be extracted by a research assistant who is unaware of group assignment (i.e. blinded outcome assessment).

Two mobility-related goals will be established at baseline by all participants using the GAS with assistance from a research assistant or health coach. Once the goals are agreed upon the research assistant or health coach and participant will then predict the GAS outcomes on a five-point scale ranging from −2 to +2, where a score of 0 indicates achievement of the set goal, a score of −1 indicates no change from the baseline level of ability for that goal type, −2 indicates worse performance than at baseline and +1 and +2 indicate ‘somewhat better’ and ‘much better’ performance than the set goal, respectively.

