### Sample size justification

A total of 130 participants (65 per group) will provide 80% power to detect a 15% between-group difference in the primary physical activity outcome (i.e., a between-group difference of 35 mean counts per minute during wear time, standard deviation of 91), a dropout rate of 15% and alpha of 5%. The estimates of mean accelerometer counts per minute for this calculation were taken from the 263 community dwelling USA-based women aged 65 and older in a large sample of accelerometer data [24]. We took a conservative approach and estimated the proportion of dropouts at 15% although our previous trials have had lower dropout rates. These calculations were undertaken in Stata 12 using the sampsi command, assuming a 0.7 correlation between measures and assuming a post-test between-group comparison that adjusted for baseline scores.

A sample size of 130 will also provide 80% power to detect a clinically meaningful 20% between-group difference in goal attainment scores. The sample size will also be sufficient to detect between-group differences in the order of 10-15% for the secondary outcome measures.

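### The 12-month accelerometer comparison, as most naturally read, ignores the 6-month values of people lost afterwards; a joint repeated-measures model would be more robust at little cost

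*Protocol article*

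**What the plan says.** The section Analysis of outcomes names the model: "General linear models will be used to assess the effect of group allocation on the continuously-scored primary (average physical activity counts per minute"). The same sentence covers quality of life, fear of falling, mood and mobility limitation, and sets the timing and covariate: "at both six and 12 months after randomisation, after adjusting for baseline scores".

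The same section gives the wear rule, "Acceptable wear time will be set a priori and defined as 4 days or more of 10 hours or more per day", and says that all analyses "will use an intention-to-treat approach".

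Two other sections bear on how the model is to be read:

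- Primary outcomes counts each visit as an outcome of its own: "The four primary outcomes will be: physical activity participation, expressed as mean counts/minute/day, assessed over a 7-day period", with activity and goal attainment each taken at 6 and at 12 months.
- Sample size justification says "A total of 130 participants (65 per group) will provide 80% power to detect a 15% between-group difference in the primary physical activity outcome". It assumes a single follow-up comparison adjusted for baseline, with a correlation of 0.7, and the sponsor "estimated the proportion of dropouts at 15" per cent.

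**The concern.** A linear model with one follow-up value as the outcome can use only people who have that value. At 12 months that leaves out those who have dropped out and, on the natural reading of the wear rule, those without enough valid days. Some of them will have a valid 6-month value, which is post-randomisation information on the same measure and probably the best available predictor of the missing one. The planned model has no place for it in the 12-month contrast.

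This matters if the chance of being missing at 12 months depends on 6-month activity, and does so differently in the two arms. The arms are treated differently in ways that could produce this. Under Intervention group, only that arm has fortnightly coaching, a feedback pedometer and monitoring of uploads, all planned for 6 months. If the less active intervention participants then drift away while control losses are unrelated to activity, the intervention participants still measured at 12 months are a favourable selection, and the 12-month effect is too large. The document neither shows nor excludes this pattern.

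**Working it through.** **1. The plan's own sample size.** Inputs from Sample size justification: difference 35, SD 91, correlation 0.7, power 80%, alpha 5% (taken as two-sided), dropout 15%.

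- Baseline-adjusted SD = 91 × √(1 − 0.7²) = 64.99.
- n per arm = 2 × (1.960 + 0.842)² × 64.99² / 35² = 54.1, so 55.
- Allowing for dropout: 55 / 0.85 = 64.7, so 65 per arm and 130 in total, as stated.

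The sample size is correct. The agreement also supports the reading of the model: N is that of one baseline and one follow-up, with about 55 people per arm in the comparison and the rest absent from it.

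**2. What goes unused.** 15% of 65 is 9.75. If all the dropout fell after month 6, about 10 six-month values per arm would have no part in the 12-month contrast. Fewer are affected if some of the loss comes earlier.

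**3. The two estimators.**

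- Per-visit: regress the 12-month value on group and baseline among people observed at 12 months, and take the group coefficient.
- Joint: let *a* be the group effect on the 6-month value given baseline. Among people observed at 12 months, regress the 12-month value on group, baseline and the 6-month value; call the group coefficient *c* and the slope on the 6-month value *s*. The 12-month effect is *c* + *s* × *a*. With two visits and loss only at the second, this is the maximum-likelihood estimate from a repeated-measures model with group-by-time, baseline-by-time and unstructured covariance.

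**4. Simulation at trial size.** 20,000 trials of 65 per arm; SD 91, true difference 35 at both visits, correlation 0.7 between all visits, 6-month data complete. Only the SD, the difference and the 0.7 come from the document. Applying 0.7 to every pair of visits, and all the missingness mechanisms, are assumptions.

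| 12-month missingness | Missing overall | Per-visit (SE) | Joint (SE) |
|---|---|---|---|
| Unrelated to anything | 15.0% | 34.9 (12.46) | 34.9 (12.32) |
| Depends on baseline, intervention arm only | 18.6% | 35.0 (12.86) | 35.0 (12.64) |
| Depends on 6-month value, same rule in both arms | 15.7% | 34.1 (12.50) | 34.9 (12.39) |
| Depends on 6-month value, intervention arm only | 16.8% | 39.1 (12.62) | 34.9 (12.50) |

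In the last row the log-odds of being missing rise by 1.5 per SD lower 6-month activity (odds ratio e^1.5 = 4.5). The gain in SE runs from 1 − 12.39/12.50 = 0.9% to 1 − 12.64/12.86 = 1.7%.

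**5. How far the last row depends on its assumptions.** Large-sample runs with weaker dependence, in the intervention arm only:

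- Correlation 0.7 throughout: per-visit effect about 36.5 at odds ratio e^0.5 = 1.6 per SD, and about 38.2 at e^1.0 = 2.7.
- Baseline correlated 0.6 with each follow-up and 0.7 between follow-ups, odds ratio 2.7: about 40.1.
- Smallest value found (0.7 with baseline, 0.6 between follow-ups, odds ratio 1.6): about 35.8.

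The joint estimator returned about 35 each time.

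**6. Size.** 36.5 − 35 = 1.5, or 4% of 35. 40.1 − 35 = 5.1, or 15%. Against an SE of about 12.5 these are 0.12 and 0.41 of an SE.

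**The case against.** Five points can be made for the plan.

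- **The text does not say separate models, or models restricted to people with valid wear.** Correct: the reading is inferred from the model named, the list of four primary outcomes and the sample-size basis. It is the most natural reading, not a stated fact.
- **A reader might infer that the analysis breaks the intention-to-treat promise.** The document does not support that. It gives the label without a definition, and analysing available outcomes by randomised group is compatible with it. Nothing excludes people for poor adherence or moves them between groups.
- **Handling of missing data may sit in a statistical analysis plan that is not shown.** So its absence from this article is no fault. The point here is narrower: the model the article does name cannot use the 6-month value for the 12-month contrast.
- **Baseline-adjusted comparison at one visit is a standard method that matches the power calculation.** It is also unbiased when missingness depends only on arm and baseline. This stands, and so a reader should not conclude that the 12-month estimate will be too favourable. With the same rule in both arms the simulated bias was about −1, slightly against the intervention.
- **The mechanism is assumed, and its rationale is not strong.** Coaching and the pedometer period end at 6 months, and the feedback device is not the outcome monitor. This also stands. It lowers the weight of the point, but the alternative costs little and gave about 35 in every scenario tried.

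**Conclusion.** The point holds in a limited form. The per-visit models, as most naturally read, leave out information the trial will already hold, and this makes the 12-month contrast less robust than it could be. The possible overstatement is about 1.5 to 5 counts/minute (4% to 15% of the design difference, under half an SE). It arises only if 12-month missingness depends on 6-month activity differently by arm, with the less active intervention participants lost. The size follows the assumed strength of that dependence and the correlations between visits: it fell below 1 in the mildest case, and a stronger dependence would give more. Under random, baseline-dependent or arm-symmetric missingness there is essentially no bias, and the precision gain does not by itself justify a change.

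The case for change is protection against one plausible pattern of loss at small cost. It is not that the plan contradicts itself, and the stated sample size is not in question.

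**What to change.** For counts/minute and the continuous secondary outcomes, specify one mixed model for repeated measures before unmasking:

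- 6- and 12-month values as outcomes;
- group-by-time and baseline-by-time terms;
- unstructured covariance;
- all randomised participants with at least one valid follow-up value, in their allocated group;
- between-group contrasts at each visit.

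Keep the per-visit baseline-adjusted models as sensitivity analyses. They match the basis of the power calculation, and a gap between the two at 12 months would itself be informative.

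The cost is a change of wording and slightly more programming, with no new data. The model rests on a missing-at-random assumption given baseline and the observed follow-up. It gains little at 6 months and adds nothing for people with no follow-up value. It does not correct missingness that depends on unobserved activity, which would need its own sensitivity analysis.

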### Recruitment and randomisation

Participants will be recruited in metropolitan Sydney and surrounds, in Australia via community-based newspaper advertisements, local council websites, and newsletters and mailing lists of established organisations for older people, commencing in January 2014. Allocation to study groups will take place after completion of baseline questionnaires, the assessment of current physical activity participation and the setting of mobility-related goals. To ensure allocation concealment, randomisation to groups will be undertaken by an investigator not involved in recruitment using a computer generated random number schedule with randomly permuted block sizes of between 2 and 6.

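### The 6-month activity model adjusts only for a baseline taken half a year earlier; a season-of-randomisation term would be a cheap, optional gain in precision

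*Protocol article*

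**What the plan says.** - **Timing of baseline** (Recruitment and randomisation): "Allocation to study groups will take place after completion of baseline questionnaires, the assessment of current physical activity participation". The baseline count is therefore taken shortly before randomisation.
- **Timing of outcome** (Primary outcomes): "Physical activity participation will be assessed at both six and 12 months after participant randomisation".
- **Model** (Analysis of outcomes): general linear models test the group effect on counts "at both six and 12 months after randomisation, after adjusting for baseline scores". No date or season term is named.
- **Allocation** (Recruitment and randomisation): a "computer generated random number schedule with randomly permuted block sizes of between 2 and 6".
- **Recruitment period** (same section): in Sydney and surrounds, "commencing in January 2014". No end is given.
- **Sample size** (Sample size justification): "A total of 130 participants (65 per group) will provide 80% power" for "a between-group difference of 35 mean counts per minute during wear time, standard deviation of 91", "assuming a 0.7 correlation between measures and assuming a post-test between-group comparison that adjusted for baseline scores".

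The article does not mention season and gives no figure for seasonal variation in counts.

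**The concern.** Baseline adjustment gains precision because a person's baseline predicts the later value. A yearly cycle works against this at 6 months. Someone recruited near a seasonal peak has a raised baseline and a lowered 6-month value, and someone recruited near a trough has the reverse. The adjustment then carries the seasonal part in the wrong direction. At 12 months the cycle has returned to the baseline season and the problem almost disappears.

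The blocks add a second feature. They balance the arms over calendar time, so the between-group difference is largely protected from season. A model without a date term does not credit that balance, and its standard error is larger than the true sampling variation.

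What is at stake is precision on one of the four primary outcomes, activity at 6 months, which is measured as the coaching period ends.

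**Working it through.** **Inputs from the protocol article.** Difference 35, SD 91, correlation 0.7, alpha 5% (taken as two-sided), dropout 15%, 65 per group. The 15% difference implies a mean of 35/0.15 = 233.

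**Inputs assumed.** A sinusoidal season of amplitude A equal to 5%, 10% or 15% of 233 (11.7, 23.3 or 35 counts/min); even recruitment over 1 to 12 months.

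**1. The plan's own figure.** n = 2(1.96 + 0.84)² × 91² × (1 − 0.49)/35² = 54.1, so 55 per arm. 55/0.85 = 64.7, so 65 per arm and 130 in total. The stated size reproduces. With 65 × 0.85 = 55.25 completers per arm, power is 80.8% and the 95% half-width is 24.2 counts/min.

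**2. The seasonal term.** Write the seasonal part as +A cos θ at baseline and −A cos θ at 6 months, where θ is the calendar date. With slope 0.7 the residual keeps −(1 + 0.7)A cos θ, or 1.7 times the swing. At 12 months it keeps (1 − 0.7)A cos θ, or 0.3 times.

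**3. Residual variance, taking 91 and 0.7 as free of season.** Let s be the variance of A cos θ over the recruitment window, which is A²/2 for a full year. Total variance is 8281 + s, covariance is 5796.7 − s, and residual variance is total − covariance²/total. With a season term in the model it is 8281 × 0.51 = 4223.

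Example at 10% amplitude, full year: s = 272.2 and residual = 8553.2 − 5524.5²/8553.2 = 4985. Then √(4985/4223) = 1.086.

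| Amplitude | s | Residual variance | Interval wider by | Half-width | Power |
|---|---|---|---|---|---|
| 0 | 0 | 4223 | 0% | 24.2 | 80.8% |
| 5% | 68.1 | 4418 | 2.3% | 24.8 | 79.0% |
| 10% | 272.2 | 4985 | 8.6% | 26.3 | 74.1% |
| 15% | 612.5 | 5872 | 17.9% | 28.6 | 67.0% |

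**4. Dependence on the recruitment window.**
- *6 months from peak to trough:* same as the full year.
- *6 months centred on a peak or trough:* s = 0.095A², so 0.4%, 1.7% and 3.8% wider at the three amplitudes.
- *3 months starting at a peak or midway between peak and trough:* again s = 0.095A², with the same 0.4%, 1.7% and 3.8%.
- *3 months centred on the steepest part of the cycle (worst placement):* s = 0.182A². At 15% amplitude the residual is 8503.6 − 5574.1²/8503.6 = 4850, and √(4850/4223) gives about 7% wider.
- *1 month:* at most about 0.9% wider.

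**5. Simulation with the stated allocation.** 130 people were allocated in blocks of 2, 4 or 6 in date order, with 15% random dropout, recruitment over 12 months and 6000 trials per setting. At 5%, 10% and 15% amplitude:
- *Baseline-only model:* power about 78–79%, 74% and 68%; type I error about 4–4.5%, 4% and 2–3%.
- *With a sine/cosine pair added:* power about 79–80% and type I error near 5% throughout.
- *No seasonal effect:* the two models agree within simulation error.

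If the blocks are ignored in the simulation, the baseline-only interval has 94.4% coverage at 10% amplitude. The conservatism therefore comes from the blocking.

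**6. The 12-month contrast.** At 10% amplitude the covariance is 5796.7 + 272.2 = 6068.9 and the residual is 8553.2 − 6068.9²/8553.2 = 4247. Intervals are 0.3% wider, which is negligible.

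**7. If 91 and 0.7 already contain season.** The baseline-only model then delivers the planned 80.8%. At 10% amplitude a season term leaves 8008.8 − 6068.9²/8008.8 = 3410, and power rises to 88.3%. At 5% amplitude it rises to 82.6%.

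**The case against.** The strongest reply is that the plan contains no error. Baseline-adjusted analysis is standard, matches the model used for the sample size, and is unbiased under this randomisation. Both quantities that drive the loss, the seasonal amplitude and the recruitment window, are assumed. Further covariates are commonly left to a statistical analysis plan, which is not shown, and the article does not say that baseline is the only one. All of this stands, and it is why the point is a suggestion and not a defect.

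A reader might infer more than the article supports:

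- **That the trial is underpowered.** The article does not say where 0.7 came from or whether it and the SD of 91 exclude season. If they include it, planned power is met (step 7).
- **That the intervals or the estimate are invalid.** The estimate is unbiased, and the standard error errs on the conservative side.
- **That every participant's 6-month value is seasonally displaced.** Under a single yearly cycle, people recruited midway between peak and trough are at about the same seasonal level six months later.
- **That all the primary outcomes are affected.** Activity at 12 months is essentially untouched (step 6), and the argument does not concern goal attainment.

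The reply does not remove the case for acting. The article itself calls the analyses pre-planned, so a season term is better named in advance than added after the data are seen.

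**Conclusion.** The mechanism is real and the loss is conditional. It requires both a seasonal effect on activity counts and recruitment spread over enough of the cycle; the article documents neither. Under the assumed range, and taking SD 91 and correlation 0.7 as season-free, the cost to the 6-month activity contrast runs from nothing to intervals about 18% wider and power of about 67–68%. With short recruitment or a small amplitude it is a few per cent or less. This is a low-severity point about efficiency on one primary outcome.

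**What to change.** In Analysis of outcomes, or in the statistical analysis plan if one exists, state that the 6-month activity-count model will include season of randomisation alongside the baseline score. Use either one sine/cosine pair of the randomisation date or a four-level quarter, and fix the choice in advance.

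The cost is one sentence and 2 degrees of freedom (sine/cosine) or 3 (quarter). No new data are needed, since follow-up is timed from randomisation and the date should be on record for everyone. If season proves irrelevant or recruitment is short, the term can stay in with negligible loss.
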